**Figure 1. Study Design**[figure not shown]**Study Design**

The design of the proposed research project is presented in Figure 1, above.

**Community youth samples.** Evaluation of the impact of the CTC intervention on youth outcomes (Aim 1) will include comparisons between the intervention and control communities on trends in risk, protection and drug use and related problem behaviors assessed through repeated cross-sectional surveys of all consenting 6th, 8th, 10th, and 12th grade public school students in each community conducted in 2004, 2006, and 2007 (SS in Figure 1). Comparisons also will be made between the intervention and control communities on individual student-level changes in risk, protection, and initiation of substance use, delinquency, and violence through annual surveys of a longitudinal panel of 200 fourth grade students in each community recruited in the first year of the project and followed throughout the project (Panel in Figure 1).

**Community key informant samples.** Evaluation of CTC's impact on community prevention service systems (Aims 2-4) will include comparisons between the intervention and control communities on measures of collaboration, use of epidemiological data to guide planning and resource allocation decisions, and selection of tested prevention strategies. Data on these measures will be obtained through interviews with key informants in each community conducted in 2004 and 2006 (CKI in Figure 1).

**Community prevention policy and program samples.** Information on the types, quality, and scope of prevention activities consistent with effective interventions for elementary and middle school-aged youths and their families (Aims 3 and 4) will be obtained through structured interviews with prevention service providers and program directors, also conducted in 2004 and 2006 (CRD in Figure 1).

**Strengths of the proposed study design.** Conducting the proposed research with 12 pairs of communities participating in the Diffusion project provides several distinct advantages. These include: 1) three waves of baseline data measuring trends in risk, protection, and adolescent substance use, delinquency, violence, and related problems from student surveys conducted in each community prior to the start of the proposed study; 2) two waves of baseline data on each community's prevention planning approach including the degree of implementation of risk- and protective-focused prevention collected prior to the start of the proposed study; 3) two waves of baseline data on the number, types, and scope of science-based prevention strategies within each community collected prior to the start of the proposed study; and 4) a five-year history of collaboration between these communities and the researchers. Another strength of the proposed design is the combination of repeated cross-sectional surveys of students in four different grade levels with a longitudinal panel of students followed and surveyed annually for the five years of the project. Using the two survey methods, which provide complementary approaches to assessing intervention impact on risk, protection, and substance use and related problem behaviors, addresses different threats to the internal validity of study findings (Salonen et al., 1986; Wagner et al., 1991). Finally, the two assessment methods focus primarily on the age group

affected most directly by the prevention strategies implemented as a result of the CTC intervention, but also allow evaluation of the impact of broader community policy and norm changes on the prevalence of problem behaviors among older youths.

### **Measurement Methods, Schedules, and Instruments:**

Since 1988, the Social Development Research Group has maintained a centralized data collection unit with extensive experience in gathering data from general population and clinical samples. The unit has interviewers and supervisors with extensive experience in various aspects of data collection, including recruitment, locating, and mail, telephone, individual in-person, and school-based, group-administered surveys. Our data collection unit has been successful in maintaining high completion rates, and in providing complete data with little missingness across items.

Cross-sectional surveys. In the spring of Project Years 2, 4, and 5, all 6th, 8th, 10th, and 12th grade public school classrooms within the intervention and comparison communities will complete the youth survey used in the Diffusion project. The cross-sectional surveys will be conducted in February of each academic year by the research subcontractor in each state using scanable forms developed and printed following specifications provided by the SDRG data collection unit. This process has been used successfully in the Diffusion project to conduct the cross-sectional surveys in that project's 41 communities.

Based on our experience in the Diffusion project, we anticipate obtaining usable data from a minimum of 70% of the public school students at each of the targeted grade levels in each community. The average single grade enrollment in 2000 across these 24 communities is 316 students, resulting in an average of approximately 221 useable surveys per grade per community. To ensure high participation rates, we have provided special monetary incentives for schools that achieve a 70% participation rate.

The effects of the elementary school interventions on risk and protective factors and early problem behavior initiation will be assessed by comparing cross-sectional sixth grade samples over time in experimental and control communities. The surveys at eighth grade (ages 13-14) provide measurement of the degree of spread of risk and problem behaviors by the end of middle school in intervention and control communities. The final eighth grade cohort (assessed in Project Year 5) will have received maximum exposure (four years) to the services implemented as a result of the CTC intervention, and the cumulative impact of the elementary and middle school interventions on the early initiation of drug use and related problem behaviors will be assessed at this grade level. The 10th grade surveys will allow detection of changes in risk, protection, and problem behaviors that result from the interventions provided during the middle school grades. Finally, the 12th grade surveys will provide a measure of community-level trends in adolescent outcomes measured at the end of high school and will allow assessment of the impact of the community-level interventions alone. This measurement design will allow for comparisons of trends across six cohorts for each age group over the five baseline years (collected in the Diffusion project) and the five years of the proposed study.

Longitudinal panel. Based on power analyses described later, a longitudinal panel of 200 students enrolled in the fourth grade in each community will be identified in the first year of the study and surveyed by SDRG data collection staff in each of the five years of the study. Representative samples of fourth grade students in each community will be recruited for participation in the longitudinal sample, and active parental consent will be obtained. Because we estimate that 280 students will be required to obtain 200 consenting panel members, the sample for the longitudinal panel will include the entire population of fourth grade public school students in the 16 communities of less than 20,000 total population in the study, and over 70% of the fourth grade students in six remaining communities. If children in this cohort in intervention communities are affected by the CTC intervention, the longitudinal panel sample should be sensitive to these effects.

Students participating in the panel who remain in the community through the second year of the project (when services resulting from the CTC intervention will be initiated in the intervention communities) will be identified and resurveyed in the spring of the second project year. Once students recruited into the panel sample have participated in the first two waves of data collection, we will track them and resurvey them annually for the remainder of the study regardless of whether they remain in the community or move elsewhere. Data obtained from the panel sample will provide a strong test of intervention effects (Salonen et al., 1986; Wagner et al., 1991). The students in the panel will receive the greatest exposure to the service and system-level changes produced by the CTC intervention. Moreover, the panel sample will allow analyses of individual characteristics, program exposure, and trajectories of risk, protection, and outcomes, and the relationship of these factors to intervention effects.

We expect to achieve an initial consent rate of 70% for the panel sample. We expect that 85% of these youth will remain in the community through the second year of the project and be retained in the panel. We expect that 90% of these youths will provide usable data in the fifth year of the study, yielding a final panel sample in each community of approximately 150 youths. Active youth and parental consent will be obtained from panel sample participants using consent-gathering techniques that have proven successful in our previous studies. The SDRG data collection staff has extensive experience obtaining high completion rates. The NIDA-funded Seattle Social Development Project (SSDP), which followed a panel of 808 students from age 10 to age 16 with extensive yearly interviews, achieved an interview completion rate of 95% (770) at age 16. Subsequent follow-up interviews of the SSDP panel have obtained completion rates of over 92% at ages 18, 21, and 24 (Battin et al., 1998; Hawkins et al., 1999).

Locating and retention. A variety of overlapping methods will be used to locate and track panel members over time, including a computer-based panel locator system, paid, on-line address database searches, telephone and reverse directory searches, and address correction mailings. Additionally, we will work with schools to track student transfers during and between school years. The panel locator database will contain information obtained during the initial consent and will include: (a) parent's Social Security Number; (b) names, addresses, and telephone numbers of multiple family members and friends of the parent and student who should know how to reach the subject; and (c) the names and addresses of the parent's employers and the schools the student has attended. If all these potential locator sources are exhausted, the parent's Social Security number will be submitted to a national on-line database service which can provide current address and telephone number information (as well as address and telephone histories), not only for the selected subjects, but also for neighboring households via reverse directories which provide telephone numbers based on address information alone. Finally, all correspondence will be sent "address correction requested" as a means of informing both telephone and on-line locating efforts.

Student survey administration. Both the cross-sectional and longitudinal surveys will be group administered during one classroom period and will take approximately 45 minutes to complete. The survey items and responses will be read to students in grades 4 and 5 so that reading ability will not be a source of bias. We will make every effort to ensure that subjects are comfortable and to assure them that their responses are confidential. We will further ensure that students do not have the opportunity to see each other's survey forms during administration. Where the students participating in the longitudinal panel constitute a sample rather than the entire grade population of students in study schools, they will be surveyed as a group in a school setting outside of their regular classrooms. As the panel moves into middle school, this procedure will be repeated. Students who move out of the study communities after the second year of the study will be tracked and surveyed individually using similar survey administration procedures and the same self-report, scannable survey instrument. These procedures will maintain parallel survey administration protocols across all participants.

We recognize that surveying students in public schools may underestimate prevalence of problem behavior by missing youths who do not attend school or may bias the estimate by missing students in private schools. However, this need not compromise the internal validity of the study if that bias is the same in both intervention and comparison communities. We will assess this threat in the cross-sectional surveys of 10th and 12th grade students by looking for differences in rates of school dropout in intervention versus control communities. Any differences observed can be addressed in analysis by adding dropout rate as a community-level covariate. Moreover, the longitudinal panel of fourth grade students will be followed regardless of their continued involvement in school.

Instrument. The Youth Survey will be used in the proposed study (See the Instrument and Item-Construct Dictionary in Appendix B, and Arthur et al., 2001; and Pollard et al., 1999 in Appendix A). This instrument measures risk and protective factor constructs in the community, school, family, and peer/individual domains as well as drug use, delinquency, violence, gang involvement, and depressive symptoms. This instrument has been used in the Diffusion project, providing three waves of cross-sectional baseline data for each community. For the proposed project, the Youth Survey will be modified for use in the fourth and fifth grade panel surveys to be developmentally appropriate. Pretesting and pilot testing of the Youth Survey for use with students in grade 5 has recently been completed for another study at SDRG and will inform modifications for the proposed study. A copy of that instrument (the International Youth Development Survey) is included in Appendix B.

Community Key Informant Interviews. To assess the level of community implementation of risk- and protective-focused prevention, telephone interviews will be conducted with key community leaders in both the intervention and comparison communities in projects years 2 and 4. The key informant

interviews will be administered by trained interviewers using computer-assisted telephone interviewing (CATI) technology. The use of CATI as a survey mode increases data quality by automating skip patterns, decreasing missingness, and eliminating out-of-range responses. A two-step reputational sampling method will be used to select approximately 15 key informants per community (Cohen et al., 1986; Wagner et al., 1991). The key informants will include experts in drug abuse and violence prevention, key community organizations and agencies involved in prevention programs, and local education, government, health, and business leaders. In the intervention communities, the Community Board will form part of the key informant sample but non-board members will also be surveyed. Special effort will be made to ensure representation of leaders of racial and ethnic minority groups and organizations. The key informant surveys will be conducted six months from the time of the Community Board surveys to reduce the burden of data collection activities.

**Instrument.** The community key informant (CKI) interview will use the protocol developed in the Diffusion project. It will include closed-ended questions to assess degree of implementation of risk- and protective-focused prevention and factors hypothesized to influence degree and rate of implementation. It will also include open-ended questions to allow respondents to describe their prevention approach and their experiences with implementation of risk- and protection-focused prevention. Specific constructs measured by the CKI interview include the respondents' ratings of their community's stage of implementation of the risk and protective prevention approach, their reports of interagency collaboration, and their reports regarding their organization's use of data to guide strategy selection, resource allocation, and program evaluation (see the Community Key Informant Interview and Item-Construct Dictionary in Appendix B).

**Community Resource Documentation.** The Community Resource Documentation (CRD) process will be used to measure the number and quality of promising prevention programs in the 24 study communities. The CRD data collection process developed for the Diffusion project is a combination of telephone interviews and mail surveys designed to document the prevention resources (policies, systems, coalitions, and laws and practices) that are in place within a community. All telephone surveys will be administered by trained interviewers using CATI technology. Mail surveys will be administered following Dillman's Total Design Method, which relies on personalization and multiple contacts to achieve high response rates (Dillman, 1991). The process begins by interviewing informants from social service agencies and prevention coalitions that have been previously identified in these communities through the Diffusion project. Mail surveys are also sent to the principal of each public elementary, middle, and high school in the community.

From the Agency, Coalition, and School Building surveys, a snowball sampling method is used to identify active prevention programs in each community. These community prevention programs are then contacted and interviewed. The focus of these interviews is to identify programs, policies, and practices that are consistent with those shown to be effective in controlled evaluation trials, and to assess the quality, scope, and target populations of these prevention activities.

The CRD data collection process will be conducted in intervention and control communities in Years 2 and 4. Respondent samples from the Diffusion project's CRD data collection efforts will be used to begin the CRD process in each community. New programs will be added as they are identified during the snowball sampling questions asked in each interview module. SDRG has developed an MS Access application that integrates the respondent tracking system and the computer-assisted telephone interviews to manage the survey sample and data during the data collection period. Respondents will be contacted first by mail and then by trained SDRG interviews by telephone to schedule and conduct the thirty-minute interviews.

**Instruments.** The Diffusion Consortium CRD survey instruments are included in Appendix B. The Agency interview collects information on the prevention staffing, funding, and the agency's collaborative prevention efforts, as well as a list of preventive programs sponsored by the agency. The Prevention Coalition interview measures any community mobilization strategies used by the community and the coalition's collaborative prevention efforts. School based prevention activities are assessed through the School Building survey administered to all public schools in the community serving K through 12th grade levels. School strategies measured in the school building survey include: (a) organizational change; (b) classroom organization, management and instructional strategies; (c) classroom curricula for social and emotional competence promotion; (d) school behavior management; and (e) school policies. The agency, coalition, and school building surveys also identify six specific types of prevention programs offered by the responding organization, and key informants for each program are identified. These include parent training, mentoring, tutoring, social competence

promotion, youth employment, and after school recreation programs. The identified program informants are then interviewed using a specific program interview module tailored to each program type. The screening criteria and quality measures for each program type used in the Diffusion project will be reviewed by the Scientific Advisory Board during the first six months of the Project to assure the validity of these criteria.

From the CRD interview process, we are able to calculate the numbers of programs of each type that are consistent with quality criteria in effective interventions, as well as measures of the scope (number and ages of youths served), dosage (total number of prevention hours offered), and overall exposure (scope x dosage) of each type of program in the community.

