The proposed study is designed to achieve widespread community activation and intensive implementation of the selected interventions. Staffing and budgetary levels have been established to ensure that intervention communities will receive adequate resources to implement widespread, coordinated interventions in multiple social domains for four years. The school and family interventions implemented in the second project year will focus on elementary schools, while those implemented in Years 3 through 5 will target middle schools as the longitudinal panel moves from elementary to middle school grades. Resources are provided to serve 2 to 4 elementary/middle school populations identified through the school survey data as having the highest aggregate levels of risk and lowest levels of protection in the community. The resources will reach at least ten classrooms, 200 students, and 100 parents each year in each intervention community. In communities of less than 15,000 residents, the resources requested will be adequate to implement new interventions for all youths in the target ages, while in the larger communities youths attending those schools identified through risk assessment as serving populations at highest risk will receive the interventions.

In addition to implementing programs targeting elementary and middle school students and their families, each community board will mobilize broad sectors of the community to work to change community norms, policies and practices regarding adolescent problem behaviors through the task force structure described earlier. This task force will address community norms by affecting policy changes and by creating the informal social impetus to strengthen the impact of such changes. The board will also involve local media in mobilizing the community and generating widespread support for the board's efforts by publicizing their mission, objectives, decisions, and activities. Media will be used to: (a) educate community members about risk and protective factors for adolescent problem behaviors; (b) communicate clear norms and enforcement policies regarding problem behavior in the community; (c) generate public support for regulatory measures; and (d) motivate community members to take part in efforts to reduce risk factors and promote protective processes in the community. Representatives of the local media will be recruited to the board to provide expertise in these efforts.

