**Including moderate-sized communities.** The communities in the proposed study have a population between 1,500 and 50,000 residents with a clear community identity and boundaries. These are small-to moderate-sized towns with their own governmental, educational and law enforcement structures. Focusing on communities within this restricted size range will limit the generalizability of study findings, but there are important methodological advantages to using towns of this size in community studies (Biglan, 1995). These communities are small enough that their prevention service systems can be clearly defined and measured. Because the enrolled student population in a single grade ranges from 40 to 506 in these communities, with only two communities exceeding 400 students per grade, the study can expose a large proportion of the early adolescent youths in the intervention communities to the chosen programs and policies at a reasonable cost without compromising the power of the experiment. The use of small-to moderate-sized communities increases the likelihood of observing effects of changes in community prevention services on the levels of risk and protective factors experienced by youths in these communities.

**Randomization.** Randomization of one member of each pair of eligible communities occurred prior to recruitment into the proposed study. For each pair, a coin toss determined which of the two matched communities was assigned to the intervention condition.

**Avoiding cross-community contamination.** It is essential to minimize the likelihood of contamination of the control communities, while ensuring that the intervention is fully implemented in intervention communities. Key leaders of control communities will be aware of the project and its requirements,

**Table 2: Baseline Comparisons Between  
Intervention ("I") & Control ("C") Communities**

| Measure                                            | I         | C         |
|----------------------------------------------------|-----------|-----------|
| 2000 Total Population                       | 15,814.25 | 13,927.50 |
| Mean                                               |           |           |
| Standard Deviation                                 | 12,446.06 | 9,824.09  |
| 2000 Percent White                          |           |           |
| Mean Proportion                                    | 88.38%    | 88.74%    |

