**Aim 2.** To examine effects of CTC on levels of collaboration across agencies, groups and organizations in communities.

**Aim 3.** To examine effects of CTC on community use of epidemiologic data to guide prevention service system planning.

Aims two and three address the effects of the CTC intervention on community-level outcomes. Community outcome analyses will be conducted using single level models since the outcomes are viewed as characteristics of the community. Since the analyses for both aims are the same, they are described together. Both cross sectional and longitudinal analyses will be conducted to assess average differences and changes in collaboration or use of epidemiological data over time as they relate to the intervention.

Differences between treatment and control communities in community-level outcomes will be assessed using standard General Linear Models (GLMs). Community covariates will be used to reduce the error

variance of each model and help explain reasons for differences between communities. Further longitudinal analyses using growth curves will assess the effects of intervention on changes in collaboration and use of epidemiologic data for strategic prevention planning over time. These growth curves can be assessed using either multilevel GLM techniques or structural equation models. The advantage of using structural models is that they allow more efficient modeling of ordinal variables providing more accurate estimates of parameters and standard errors (Muthén et al., 1997). These analyses will also utilize the information available for these communities for the five years prior to intervention. One method, as described above, for looking at student outcomes, is to use the slopes and intercepts from the baseline period as predictors of the slopes during the intervention period. This allows for assessing whether the intervention is able to change trajectories across time.

As in the first aim, comparisons of treatment and control communities will be elaborated by separate analyses testing the extent to which CTC implementation relates to these community-level outcomes.

**Aim 4.** To assess the degree to which the use of tested effective programs in communities predicts changes in community-wide levels and trajectories of risk, protection, and drug use and related health and behavior outcomes.

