Analyses for this aim are similar to those in Aim 1; the outcomes are measures of risk and protection and substance use and delinquent behavior at the student level and both cross-sectional models examining the relationships year by year and longitudinal models at the community level will be tested. Three- and four level HLM analyses will be used to assess these relationships as discussed above. We will begin by examining the overall relationship between total number, scope, dosage, and exposure of tested programs across all categories, as described above in the measures section, to composite measures of risk, protection, and outcomes. We will then elaborate these tests by examining the number, scope, dosage, and exposure of specific types of prevention programs (e.g., parenting skills training) and their relationship to changes in specific risk and protective factors (e.g., family management problems, parent-child bonding, etc.). We will also elaborate these tests by examining these relationships at the school building, rather than community level. The use of continuous and ordinal level predictors does not affect the specification of the multilevel models described above.

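### The Aim 4 programme measures are community totals with no denominator: scope largely tracks community size, and exposure mixes size with the programme hours each child receives

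*Protocol*

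**What the plan says.** The last paragraph on Community Resource Documentation (Measurement Methods, Schedules, and Instruments) sets out what is computed from the provider interviews. Scope is how many youths are served, with their ages. The other two measures are "dosage (total number of prevention hours offered), and overall exposure (scope x dosage) of each type of program in the community".

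Under Analysis, Aim 4, these become predictors. The analysis starts from the "overall relationship between total number, scope, dosage, and exposure of tested programs across all categories" and relates it to composite measures of risk, protection and outcomes. It then repeats this by programme type and at the level of the school building. The aim is to learn whether use of tested programmes "predicts changes in community-wide levels and trajectories of risk, protection, and drug use and related health and behavior outcomes". Those outcomes are measured on students, as scale scores and yes/no behaviours.

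Under Sample, the paragraph on moderate-sized communities says that "the enrolled student population in a single grade ranges from 40 to 506 in these communities". Nowhere is scope, dosage or exposure divided by enrolment or by the number of eligible youths. Community size is not named as a covariate for Aim 4. The example given under Aim 1 is an indicator of poverty, and community-level covariates are to be kept few.

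**The concern.** A student-level outcome should respond to how much programme a typical student receives: the share of youths reached and the hours each one gets. A count of youths served carries that information only after division by the number who could have been served. Without the division, a large town that reaches part of its youth scores above a small town that reaches all of them.

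Two things are at stake. First, the Aim 4 coefficient is confounded with anything else that differs between small and large towns. If larger towns serve more youths but a smaller share, a real benefit of coverage could be diluted or could appear with the wrong sign. Second, if these measures serve as the mediator in the test of the CTC framework, a poor measure of programme use would leave part of the treatment effect unexplained, even if CTC worked entirely through programmes.

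**Working it through.** The Protocol states no figure for this point that could be reproduced. The check uses its own ranges.

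**Inputs**
- Students per grade: 40 to 506 (Sample, moderate-sized communities). Average: 316 (Cross-sectional surveys).
- Target grades: 5 to 8, so four grades.
- Expected reach (Racial and Ethnic Composition of the Sample): all grade 5–8 students in an intervention community with 200 or fewer per grade, and two-thirds where there are more than 200.

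**Step 1. Size range.** 506 / 40 = 12.65.

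**Step 2. Raw scope against coverage under the reach assumption.** Eligible = 4 × grade size. Scope = eligible × share reached.

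| Students per grade | Eligible, grades 5–8 | Raw scope | Coverage |
|---|---|---|---|
| 40 | 160 | 160 | 100% |
| 200 | 800 | 800 | 100% |
| 316 | 1,264 | 843 | 67% |
| 506 | 2,024 | 1,349 | 67% |

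From the smallest to the largest, scope rises 1,349 / 160 = 8.4-fold while coverage falls by one-third. The section on the intervention agrees in direction: communities of less than 15,000 residents can serve all youths of the target ages, and larger ones serve the schools at highest risk.

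Simulations of this rule used 12 or 24 communities with grade size drawn uniformly or log-uniformly from 40 to 506. Scope had a rank correlation of about 0.97 to 0.98 with size and about −0.7 with coverage. These are illustrative. The uniform draw, for example, has mean (40 + 506) / 2 = 273, not 316.

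**Step 3. Exposure when every child receives the same programme.** Let N youths all be served and each receive h hours, so the dose per eligible child is h everywhere.
- If hours offered means the length of the programme, exposure = N × h. The ratio between the extremes is 12.65.
- If hours are summed over parallel groups of m youths, total hours = (N / m) × h and exposure = N² × h / m. The ratio is 12.65² = 160.

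The wording does not say which count is meant. Size enters exposure on both.

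**Step 4. Exposure when coverage and hours vary.** Assumptions: coverage spread over 20–100% or 50–100%, with and without a cap on numbers served, and log-SD of hours per child 0.3 to 1.0. The rank correlation of raw exposure was about 0.4 to 0.9 with size and about 0 to 0.8 with dose per eligible child. The more hours differ between communities, the more exposure reflects dose.

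**Step 5. Within matched pairs.** With the same assumptions and a log-SD of 0.2 for each community's size around its pair's level, differences in exposure correlated about 0.7 to 0.96 with differences in dose per child, and about 0.1 to 0.5 with differences in size.

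**The case against.** The strongest reply is that pairs were matched on size and the Aim 4 models keep the pair as a level. Step 5 shows that this helps a good deal for contrasts within pairs. It does not settle the matter. A random pair intercept does not centre a continuous predictor, so size differences between pairs still enter the coefficient. The school-level analyses are described as unmatched. Covariates are allowed, but size is not among those named.

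A second reply is that scaling a predictor is detail for an analysis plan. That would hold if the definition had been left open. Here scope, dosage and exposure are each defined, and the same measures are named as predictors.

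Several stronger readings are tempting and are not supported:
- **That the measures reflect size and not dose at all.** This is close to true for scope under the reach assumption. It is too absolute for exposure (Step 4).
- **That exposure counts size twice.** This holds only if hours are summed over parallel groups.
- **That coverage in larger communities is only 10–16%.** A reader could get this by dividing 200 students by 2,024 or 1,264 eligible youths. But the text says "at least ten classrooms, 200 students, and 100 parents each year in each intervention community", which is a floor, and the section on ethnic composition expects two-thirds.
- **That exposure is the mediator.** The mediation text speaks of community-level outcomes such as use of science-based strategies and does not name scope × dosage.
- **That the interview form records only total hours.** The instruments are in an appendix that is not shown.

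**Conclusion.** The point holds for the measures as defined. Totals without a denominator are used to predict student-level outcomes across a 12.65-fold range of grade size. Raw scope largely tracks size and can run opposite to coverage: 8.4 times higher at the largest grade size with one-third less coverage. Exposure is a mixture of size and dose per child, and its distortion at equal programme per child is 12.65-fold or up to 160-fold, depending on how hours are counted.

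The 8.4-fold figure rests on the Protocol's planning assumption about reach, not on observed data, and treats one programme as reaching that share. It compares the extremes of all 24 communities, and the text does not say which arm they are in. Only two communities exceed 400 per grade, so contrasts with 506 are not typical. The correlations rest on assumed spreads. Aim 4 is observational, and the randomised comparison in Aim 1 is unaffected. The change is worth making because it improves the Aim 4 predictors at little cost.

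**What to change.** For the Aim 4 analyses, and for the mediation model wherever these measures serve as the mediator, define:
- **scope** as youths served divided by enrolled youths in the targeted grades;
- **dosage** as hours offered per participant;
- **exposure** as the product, that is, programme hours per eligible youth.

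Two towns that give every child the same programme then score equally. State how hours are counted, per programme or summed over groups, so that hours per participant can be derived.

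Leave the number of programmes as a count. Dividing it by enrolment would create a new size artefact: one universal programme in each town would score 100 × 1/160 = 0.63 per 100 youths in the smallest and 100 × 1/2,024 = 0.05 in the largest. Report the raw totals descriptively.

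The cost is small. Enrolment by grade is already held, since the Sample and Cross-sectional surveys sections both cite it. The rest is wording, plus a check that the interviews yield hours per participant.
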